#### Hypotheses on secondary outcome

*Hypothesis 4:* At time of measurement t4 the children in intervention A show a better cognitive and motor development compared to the children in intervention B (measured by Bayley Scales of Infant Development II).

*Hypothesis 5:* At time of measurement t5 the children in intervention A show a better relationship to their primary caregiver (mother) compared to the children in intervention B (indicator: parent–child-interaction measured by the Emotional Availability Scales, EAS).

*Hypothesis 6:* The children in intervention A show after 1 year in kindergarten (t6) more often a secure attachment style (Type B) compared to the children in intervention B (measured by the Manchester Child Attachment Story Task, MCAST).

The second set of hypotheses assumes that intervention A is more effective in terms of the mothers’ psychosocial integration and language development than intervention B.

#### Hypotheses on primary outcome

*Hypothesis 7:* At time of measurement t5 more mothers in intervention A successfully have completed the integration course in comparison to those in intervention B (measured by the Integration Questionnaire with repeated assessment of questions of the BAMF questionnaire)

*Hypothesis 8:* At time of measurement t5 the mothers in intervention A are socially more oriented towards the host country, in comparison to those in intervention B (measured with the Hertie Belonging Scale).

#### Hypotheses on secondary outcome

*Hypothesis 9:* At time of measurement t5 the mothers in intervention A show a higher satisfaction with the intervention in comparison to the mothers who took part in intervention B.

### Design

Figure 2 summarizes the study design. The individual participants (children and their parents) were not aware of their group assignment, that is, if they were participating in intervention A (FIRST STEPS) or in intervention B. The integration courses which the women are attending are randomly assigned to the two different interventions A and B, because women from the same integration course cannot be referred to different interventions (cluster-randomization).

**Fig. 2 Fig2:**
[figure not shown]
Research design

### Outcome

#### Primary outcome

One primary outcome criterion is the *stress level of the children* measured by the children’s hair cortisol level a week before kindergarten entrance, 6 weeks afterwards as well as 1 year afterwards. Measuring the concentration of cortisol in hair is a new and promising method to measure cortisol (Stadler and Kirschbaum 2012). For many years cortisol was obtained primarily from blood plasma or urine, whereas later approaches added saliva and feces for non-invasive monitoring of HPA functioning. These methods are limited in the temporal range of assessment and are only snapshots of HPA activity. However being incorporated into the growing hair, hair cortisol concentrations are assumed to provide a retrospective reflection of integrated cortisol secretion over periods of several months (Stadler and Kirschbaum 2012). Over the past years supportive evidence has accumulated regarding several fundamental characteristics of hair cortisol concentrations, including its validity as an index of long-term systemic cortisol levels both in animals (Fairbanks et al. 2011) and in human participants (Manenschijn et al. 2011), its reliability across repeated assessments (Stadler et al. 2012) and its relative robustness to a range of potential confounding influences (Stadler and Kirschbaum 2012).Another primary outcome criterion is the *children’s knowledge of the German language*, assessed a year after kindergarten entrance by a trained linguist with the help of the LiSe-DaZ (Linguistische Sprachstandsdiagnostik - Deutsch als Zweitsprache, Schulz and Tracy 2011), a standardized language test. Language acquisition is critical for the children’s later school success (Gantefort and Roth 2010; Niklas et al. 2011). The LiSeDaZ enables to measure children’s development in core grammatical areas and offers separate norms for multilingual children, which take into account the age of first exposure and the length of exposure to the German language (Schulz and Tracy 2011).A third primary outcome criterion is the *children’s socio-emotional development*, evaluated at kindergarten age by kindergarten teachers using the Strengths and Difficulties Questionnaire (SDQ, Becker et al. 2004a). With the help of the SDQ the following subscales can be assessed: prosocial behavior, hyperactivity, emotional problems and conduct problems with peers. The SDQ is not only a practical and economical, but also a valid and reliable questionnaire for use in the framework of a multi-dimensional behavioural assessment, and appears to be well suited for screening purposes, longitudinal monitoring of therapeutic effects, and scientific research purposes (Becker et al. 2004b; Klasen et al. 2000; Woerner et al. 2002).A fourth primary outcome criteria on the part of the mothers is the *mother’s integration* (among others mothers’ successful completion of integration courses, employment/occupational comeback, interest in host country), measured by the repeated assessment of a part of the BAMF questionnaire and the Hertie Belonging Scale at the end of the intervention as indicators of successful integration.

#### Secondary outcomes

The secondary outcomes are:*The children’s cognitive and motor development*, assessed by trained psychologists at age 2 (t4) using the German version of the Bayley Scales of Infant Development II (BSID, Reuner et al. 2007). The BSID II evaluates infants along three scales: a cognitive, a motor and a behaviour scale. The scales have been used extensively worldwide to assess the development of infants and are known to have high reliability and validity (Vohr et al. 2012).*The emotional quality of the of mother-child interaction*, assessed at four different times of measurement (t2 to t5) by independent and trained psychologist using the Emotional Availability Scales (EAS, http://emotionalavailability.com). The EAS allow for a detailed look at caregiver-child interactions by rating the dyad on six dimensions, four focusing on the parent’s behaviour (sensitivity, structuring, non-intrusiveness, non-hostility) and two focusing on the child’s behaviour (child responsiveness, child involvement of the caregiver). Significant findings have been reported about the positive relationship between parental EA and children’s attachment security (Biringen 2000) and there is a large body of empirical research using the EA Scales (Biringen et al. 2014). It is of particular relevance that the EAS dimensions can be rated independently of the caregivers’ cultural background (Biringen 2009; Biringen et al. 2014). Ziv et al. (2000) for example reported cross-cultural applicability of the EAS by examining links with attachment. In addition the EAS are an instrument that is sensitive to change related to a program of intervention (for an overview see Biringen et al. 2014).*The children’s attachment style*, assessed by trained psychologists using the MCAST (Green et al. 2000) 1 year after entering kindergarten (t6). The MCAST, a narrative story stem task that involves playing with dolls, is a validated, structured measure that evaluates young children’s attachment representations through the use of play scenarios allowing for differentiation between four overall attachment classifications: secure attachment, insecure-ambivalent attachment, insecure-avoidant attachment und insecure-disorganized attachment representations.*The mothers’ satisfaction with the intervention,* assessed after the intervention by using a half-standardised questionnaire in form of a resumeé interview at t5.

### Sample size calculation - power analysis

The sample size calculation resp. power analysis is based on *α* = 0.05 at a power of 0.80, using pilot data concerning the number of participants in the language courses. Concerning the different primary outcomes (children’s stress level, language development, socio-emotional development and mothers’ integration) we expect effect sizes of at least *d* = 0.5. Then the sample size for analysis of variance in a RCT study would be *n* = 63. But we applied a CRCT study. Therefore we have to correct the *n* in a corrected *n** according to the following formula introduced by Eldridge et al. (2006), providing a conservative estimate of sample size requirements for trials using cluster-level analyses weighted by cluster size:$$ n* = \left\{\ 1 + \left[\ \left(1+CV{}^2\right)\ \mathrm{x}\ \mathrm{m}\ \hbox{--}\ 1\ \right]\ \mathrm{x}ICC\right\}\ \mathrm{x}\ n $$

The formula consists of the coefficient of variation *CV* for trials with unequal cluster sizes (that means with unequal sizes of language courses) and the intraclass-correlation coefficient *ICC* within the clusters and the mean cluster size *m*. Using the findings of a pilot study, the estimated coefficient of variation is *CV* = 0.4 (rather smaller) and the estimated intra class correlation coefficient (based on the pre-post differences including the *CV*) *ICC* = 0.1 (rather smaller). Furthermore, we expect a mean cluster size of *m* = 2 pregnant women in each course (cluster).

The corrected sample size would therefore be *n** = 1.132 × 63 = 71.32. Thus the minimum sample size would be 72 pregnant women per treatment and resp. 36 integration courses should be selected per treatment. However under consideration of a 20 % drop-out rate the corrected minimum sample size is *n** = *n** × 1.25 = 90 women per treatment and thus a number of 45 courses per treatment should be selected (see Fig. 2).

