**Discussion:**

The project aims at evaluating the implementation as well as the short- and long-term effectiveness of psychoanalytically oriented intervention A compared to the outcomes of intervention B. It is expected that professionally supported early parenting (intervention A) improves the social-emotional, cognitive and language development of immigrant children as well as the social integration of their families to a greater extent than in the comparison groups. In case the model project proves to be effective, a rollout across Germany is possible. Due to the “difficult-to-reach” immigrant families challenges in recruitment, uptake and retention of participants are anticipated.

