#### Hypotheses on primary outcome

The primary outcomes will be measured shortly after entering (t5) and after 1 year of kindergarten (t6).

*Hypothesis 1:* When entering kindergarten (t5) and after 1 year in kindergarten (t6) the children in intervention A show lower levels of stress compared to the children in intervention B (cortisol level measured by hair cortisol).

*Hypothesis 2:* After 1 year in kindergarten (t6) the children in intervention A show a better language development compared to the children in intervention B (measured by the Linguistic Language Development Survey – German as Second Language, LiSe-DaZ).

*Hypothesis 3:* After 1 year in kindergarten (t6) the children in intervention A show a better socio-emotional development compared to the children in intervention B (measured by the Strengths and Difficulties Questionnaire, SDQ).

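### Four unranked primary outcomes (five hypotheses) are sized at one undivided two-sided 0.05, and no success rule is tied to the effectiveness conclusion

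*Protocol article*

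**What the plan says.** **Primary outcomes.** The *Primary outcome* section lists child hair cortisol, German language (LiSe-DaZ) and socio-emotional development (SDQ). It then adds a maternal one: "A fourth primary outcome criteria on the part of the mothers is the" mother's integration. None is ranked above another.

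**Primary hypotheses.** The two *Hypotheses on primary outcome* sections give five: H1 (cortisol, at t5 and at t6), H2 (LiSe-DaZ, t6), H3 (SDQ, t6), H7 (completion of the integration course, t5) and H8 (Hertie Belonging Scale, t5). All predict an advantage for A.

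**Sizing.** *Sample size calculation - power analysis* sets alpha at "0.05 at a power of 0.80, using pilot data concerning the number of participants in the language courses". One effect size covers the whole set: "Concerning the different primary outcomes (children’s stress level, language development, socio-emotional development and mothers’ integration) we expect effect sizes of at least" d = 0.5. The result is 63 per arm, then 72 after the design effect, then 90 after 20% drop-out.

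**Analysis.** *Statistical analysis* names ANOVA and ANCOVA in a repeated-measures design. It states no test level and no order among the primary outcomes.

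**Use of the result.** The abstract's *Discussion* says: "In case the model project proves to be effective, a rollout across Germany is possible". The main *Discussion* makes a similar link to use in other cities.

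**The concern.** One alpha and one power figure are applied to several outcomes of equal standing, and one overall judgement is attached to the set. The article does not say whether one success, all successes or some ordered subset would support that judgement.

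The two simplest readings fail in different ways. If one significant result is enough, the chance of a false claim across the set exceeds the level used for sizing. If all must be significant, the false-claim rate is controlled but 0.80 is not the power of the trial. Either way, a reader of the final report could not tell how strong the evidence behind an effectiveness claim was meant to be.

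**Working it through.** **1. Reproduce the plan's figures.** Inputs, all from the sample size section: d = 0.5, alpha 0.05, power 0.80, CV = 0.4, ICC = 0.1, m = 2, drop-out 20%.

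- Per arm, two-sided: 2 × (1.960 + 0.842)² / 0.5² = 62.8, so 63. A one-sided 0.05 would give 50, so the plan's figure implies a two-sided test.
- Design effect: 1 + [(1 + 0.4²) × 2 − 1] × 0.1 = 1.132; 1.132 × 63 = 71.32, so 72.
- Drop-out: 72 / 0.80 = 90.

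The chain reproduces exactly, with alpha undivided.

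**2. Count the tests.** There are five hypotheses. If H1 is tested separately at t5 and t6 there are six comparisons; if the two times are combined in one repeated-measures test there are five.

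**3. If any one success counts and A and B do not differ on any outcome.** Each test is taken at two-sided 0.05. The correlation of 0.5 is my assumption (equicorrelated normal statistics, simulated).

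| | Five tests | Six tests |
|---|---|---|
| Any significant result, independent: 1 − 0.95^k | 22.6% | 26.5% |
| Any significant result, correlation 0.5 | 18.4% | 20.8% |
| Any result favouring A, independent: 1 − 0.975^k | 11.9% | 14.1% |
| Any result favouring A, correlation 0.5 | 9.2% | 10.4% |

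For one two-sided test, the nominal rate in favour of A is 2.5%.

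**4. If all must succeed.** Under independence with 0.80 each: 0.8⁴ = 0.41 for four outcomes and 0.8⁵ = 0.33 for five hypotheses. Positive correlation raises both, to at most 0.80.

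**5. If alpha is adjusted at the planned size.** With 72 analysed per arm, the effective number is 72 / 1.132 = 63.6. By the normal approximation, power is Φ(0.5 × √(63.6 / 2) − z) = Φ(2.820 − z):

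- alpha 0.05 (z = 1.960): 0.805
- alpha 0.0125 (z = 2.498): 0.63
- alpha 0.01 (z = 2.576): 0.60

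The t distribution gives slightly less: 0.80, 0.61 and 0.58.

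**6. Size needed for 0.80 at a Bonferroni level.** Before clustering, after the design effect and after drop-out: 90, 102 and 128 per arm for four tests; 94, 107 and 134 for five; 97, 110 and 138 for six. The plan has 90 after drop-out.

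**The case against.** The best defence is that a journal article need not carry the multiplicity procedure, and an analysis plan not shown here may hold it. The absence of a Holm or gatekeeping paragraph is therefore not the point. What remains is something the article does state: a sample size and power built on an undivided 0.05 for all primary outcomes together. A later rule can settle how the tests are read, but if it adjusts alpha or requires every outcome to succeed, the 0.80 printed here does not describe it.

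The article can also be read as making separate claims, outcome by outcome, for children and for mothers. On that reading no any-one-wins inflation arises, and 0.80 per outcome is a fair description. The rollout wording is also only permissive. This has weight, and it is why the error figures above are conditional.

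Several stronger readings are tempting but unsupported:

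- **A one-in-four chance that an effectiveness verdict is false.** The 22.6% to 26.5% is the chance of any significant result, in either direction, when nothing differs. How often a positive verdict is wrong also depends on the true effects and the power, which the article does not allow one to compute.
- **Every test is planned at 0.05.** That level is stated for the sample size only; treating it as the test level is an inference.
- **At least six tests.** Repeated-measures analysis could make cortisol one test, so five or six is the supportable count.
- **Four SDQ subscales as four primary tests.** The subscales describe what the instrument can measure; H3 is one socio-emotional comparison.

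**Conclusion.** The point holds in a limited form. Four primary outcomes of equal rank, with five hypotheses, share one undivided two-sided 0.05, and the effectiveness conclusion is not tied to any of them. The stated 0.80 is correct only per outcome at an unadjusted 0.05.

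If one success suffices, a false finding in favour of A has roughly a 9% to 14% chance instead of 2.5%, over the range from correlation 0.5 to independence. If all must succeed, joint power under independence is 0.33 to 0.41.

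These figures assume that all nulls are true (error rates) or that d = 0.5 holds for every outcome (power). The latter is only nominal for H7, which is binary. The correlation between outcomes is not given in the article.

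**What to change.** Before any analysis:

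1. Reconcile the cortisol times. H1 names t5 and t6, whereas *Primary outcome* lists three samples (a week before kindergarten entry, six weeks after and one year after). Define one primary cortisol test.
2. Limit the primary family to H1 (one test), H2, H3, H7 and H8. Integration items that no hypothesis covers, such as employment, should be secondary.
3. Control that family by a prespecified fixed order or by Holm, and state that the effectiveness conclusion rests on that procedure.
4. Restate the power in the sample size section. A fixed order keeps 0.80 for the first hypothesis, with later ones tested only if those before them succeed. Holm gives about 0.6 per test at its smallest step (0.01 for five hypotheses, 0.0125 for four) with the planned 90 per arm.

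The cost is a change of wording and a less favourable power statement. No more families are needed unless the sponsor wants 0.80 at the strictest step, which for five tests would take about 134 per arm.

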#### Intervention A - FIRST STEPS

The psychoanalytically trained FIRST STEPS project staff, mostly mothers with an immigrant background themselves, support the women (and their husbands) ideally already during pregnancy. Hence they build an emotional relationship with them in order to continue their support after the birth of the child. This support should help the women to avoid withdrawal into isolation. Afterwards the project staffs continue to accompany and support mothers and children both in group contacts (moderated weekly groups with two project staff members) and individual contacts (via telephone, home visits) until the children enter kindergarten at the age of around three. The FIRST STEPS approach is curriculum-based. The training of the project staff includes psychoanalytic case-supervision, practice reflection with the coordinator of the practical implementation^5^ as well as regular supervision with child and adolescent psychotherapists. The manualised curriculum, which has been developed by the coordinator of the practical implementation, is based on psychoanalytic and empirical developmental psychology and will be published in the near feature. The conceptualisations closely refer to other already evaluated psychoanalytically oriented parenting programs (Emde and Robinson 2000; Meurs et al. 2006; Parens et al. 1995). The training sensitizes staff for the processes of transference and counter-transference allowing for a deeper understanding of the women’s situation and children’s needs. The project staffs learn to develop a psychoanalytical “mind-set” and to create a holding and containing function (Bion 1963) in contact with the individual women as well as during the group sessions. Thus they can serve as role models and as a “secure base” (Bowlby 1969, p. 325) for the mothers, supporting them in the vulnerable phase of their early motherhood. Their consultation focuses on individual needs of the mothers and children as well as questions and concerns the families might have concerning the child’s development. The project staff thereby supports parenting competences (e.g. reflective functioning, adequate emotion regulation). Furthermore, questions concerning migration problems of the families (supporting them to consult institutions, clinics, social and mental health care services, language courses, educational institutions etc.) are addressed. Coping with losses associated with the women’s and families’ migration is supported.

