#### Intervention B

The mothers and children in intervention B take part in self-organized open “mother-child groups” led by female paraprofessionals with an immigrant background^6^, who are mostly mothers themselves, pass on their experiences to the mothers and invite for social exchange. The paraprofessionals are only instructed and informed about the study very basically, including the aimed duration of the intervention until children enter kindergarten and research instruments, and are free to conduct and organize their groups according to their views and their experience as immigrants and mothers. They do not receive any support with regard to contents and have no contact with the project organization and implementation other than with the research team collecting data about mothers and children.

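### The design effect covers integration courses of about two women but not the mother-child groups that deliver both programmes for about three years, so the 80% power is likely overstated

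*Protocol article*

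**What the plan says.** The Sample size calculation section of the protocol article takes the integration (language) course as its only cluster. It states that "we expect effect sizes of at least *d* = 0.5" for the primary outcomes and that "the sample size for analysis of variance in a RCT study would be *n* = 63". It then applies a design effect for unequal clusters, in which "the estimated coefficient of variation is *CV* = 0.4 (rather smaller") and the ICC is 0.1. On the remaining input it says "Furthermore, we expect a mean cluster size of" two women per course. This leads to 72 evaluable and 90 recruited women per arm, from 45 courses per arm.

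The Interventions sections describe a different unit of delivery. Intervention A includes "group contacts (moderated weekly groups with two project staff members"), alongside telephone contacts and home visits. Intervention B consists of open mother-child groups "led by female paraprofessionals with an immigrant background", who decide for themselves how to run them. Both programmes last from pregnancy until kindergarten entry, about three years.

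The article does not give the size, number or composition of the groups, or the number of leaders. The Statistical analysis section names ANOVA and ANCOVA with intervention as the main factor and the baseline value as the next factor. It mentions neither course nor delivery group.

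**The concern.** Families who share leaders and peers for about three years may have correlated outcomes. With about two women per course, a weekly group with two moderators could hardly be filled from one course. The alternative would be some 45 separate groups per arm averaging two mothers before drop-out. Recruitment is from three centres in one city, which makes combining courses practicable. The delivery group is therefore very likely a larger cluster than the one in the calculation.

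If so, the design effect is built on too small a unit. The variance of the treatment contrast would then be understated, power would be lower than stated, and a test that accounts for course only would be anti-conservative. The Discussion also wants differences to be attributable to the type of intervention. That attribution is weaker if between-leader variation is not separated out.

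**Working it through.** **Inputs from the protocol article (Sample size calculation):** alpha 0.05, power 0.80, d = 0.5, CV = 0.4, ICC = 0.1, m = 2, drop-out 20%. Sidedness is not stated; two-sided is inferred because it gives 63 per arm (one-sided gives 50).

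**Assumptions, not in the article:** 4 to 12 trial families per delivery group, group ICC 0.01 to 0.10, and the course CV of 0.4 carried over to groups.

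**Step 1: reproduce the plan.**
- n = 2 × (1.96 + 0.8416)² / 0.5² = 62.8, rounded up to 63 per arm.
- DE = 1 + [(1 + 0.4²) × 2 − 1] × 0.1 = 1 + 1.32 × 0.1 = 1.132.
- 63 × 1.132 = 71.32, rounded up to 72; 72 × 1.25 = 90.
- Power at 72 evaluable: Φ(0.5 × √(72/1.132/2) − 1.96) = 0.805.

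The plan's figures are correct for the cluster it chose.

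**Step 2: reserve.** 80% power needs an effective n of 62.8 per arm, so the largest tolerable DE is 72/62.8 = 1.147, against 1.132 used. At the plan's ICC and CV, 1 + (1.16m − 1) × 0.1 = 1.147 gives m = 2.1. At m = 8 the limit is reached at ICC = 0.147/(1.16 × 8 − 1) = 0.018.

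**Step 3: delivery group replaces the course as the cluster.** DE = 1 + (1.16m − 1) × ICC; power = Φ(0.5 × √(72/DE/2) − 1.96).

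| Group size m | ICC 0.01 | ICC 0.02 | ICC 0.05 | ICC 0.10 |
|---|---|---|---|---|
| 4 | 0.838 | 0.825 | 0.788 | 0.729 |
| 6 | 0.830 | 0.809 | 0.750 | 0.661 |
| 8 | 0.822 | 0.794 | 0.713 | 0.602 |
| 10 | 0.814 | 0.778 | 0.679 | 0.552 |
| 12 | 0.806 | 0.762 | 0.647 | 0.509 |

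For example, at m = 8 and ICC 0.10, DE = 1 + 8.28 × 0.10 = 1.828, effective n = 72/1.828 = 39.4 and power = 0.602. At ICC 0.05, DE = 1.414, effective n = 50.9 and power = 0.713.

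These are normal approximations. At m = 8 there would be 2 × 72/8 = 18 groups. A noncentral t with 16 degrees of freedom lowers power to 0.659 (ICC 0.05) and 0.550 (ICC 0.10).

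**Step 4: group effect added to the course effect.** With equal group sizes for simplicity, DE = 1.132 + (m − 1) × group ICC. At m = 8 this gives:
- ICC 0.02: DE 1.272, power 0.758
- ICC 0.05: DE 1.482, power 0.693
- ICC 0.10: DE 1.832, power 0.601

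**Step 5: type I error if only course clustering were modelled (conditional).** 2 × [1 − Φ(1.96 × √(1.132/DE))] at m = 8 gives 0.079 for DE 1.414 (ICC 0.05) and 0.123 for DE 1.828 (ICC 0.10).

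**The case against.** The stated sample size reproduces exactly, and the article nowhere says how large the groups are or that they combine courses. A reader might infer that groups must combine courses and that 80% power is therefore not delivered. The document supports neither as fact. Combining courses is a strong inference only, and if a group ICC of 0.01 replaces the course effect, power is 0.80 or more at every size examined.

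The CV and ICC are borrowed. Both were estimated for courses, and the text does not say whether the pilot ICC already reflects shared groups. Some features may also reduce group-level correlation. Intervention A has a manualised curriculum, supervision and individual contacts. Language and socio-emotional outcomes are measured 8 to 14 months after kindergarten entry, when the groups have ended. Open groups in B may include mothers outside the trial.

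A reader might also conclude that the planned analysis has an inflated type I error, or that a few leaders could produce the whole difference. Neither follows. The Statistical analysis section is a short summary, the full analysis plan is not shown, and the sample size formula was chosen for cluster-level analyses. The number of leaders is not stated.

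These points limit certainty and size, and they stand. They do not remove the mismatch: even if the pilot ICC includes shared groups, it is multiplied by a cluster size of two only.

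**Conclusion.** The point holds in a conditional form. The sample size calculation allows for clustering by course but has no term for the groups through which both programmes are delivered, and its reserve is very small (tolerable DE 1.147, used 1.132). Power is likely overstated. How far depends on two figures the article does not give. For 4 to 12 trial families per group, with the group replacing the course, the shortfall is material at ICC 0.05 to 0.10. At ICC 0.01 to 0.02 there is little or none for groups up to about 8. If the group effect adds to the course effect, a group ICC of 0.02 at size 8 already brings power to about 0.76. A type I error of about 8 to 12% would arise only with a group ICC of 0.05 to 0.10 at size 8 and a model limited to course clustering. It is a risk to guard against, not a demonstrated defect of the analysis.

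**What to change.** - Record the delivery group and leader for every family. The Discussion commits to documenting the number and timing of sessions and contacts but does not mention group or leader identity, which may be hard to recover later.
- Include the delivery group as a random effect, with course as a lower level where it can be estimated, and use small-sample degrees of freedom.
- State the expected group size and the number of groups and leaders. Restate the design effect and power for 72 evaluable women per arm over a stated range of group sizes and group ICCs, with the group replacing the course and with both levels present.

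No extra families are needed. The cost is a little data capture, one more variance component and a less favourable stated power.
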